### 9.4 Secondary outcome variables

Length gain: same calculation as for primary outcome

Gain in head circumference: same calculation as for primary outcome

### 9.5 Sample size calculation

Based on previous publications and own data we can expect the children to grow on average 30 grams per day with a standard deviation of 6 grams between birth and 4 months of life. Growth studies should be designed to have a power to detect a difference in weight gain equal to 0.5 standard deviations according to the SCF report. Thus, one would need about 70 children in each formula group under the assumption of non-inferiority (one-sided test), a

significance level of 2.5% and a power of 85%. We expect a true loss-to follow-up of about 10-15%. Additionally, we expect that another 15% will switch formula due to preference changes which usually take place in the first months of life. These children will be only available for an intention-to-treat analysis. Thus, 100 children in each formula arm, as well as in the breastfed group will be included to have also sufficient power in a per-protocol analysis.

## 9.6 Randomisation

The Study Formula Random Numbers are computer generated to assure an equal and random distribution of study formula to the two different formulas helping to eliminate bias that could be introduced through a selective placement of study formula.

The study formula randomisation will be a permuted-block design to achieve equal numbers in each group. A block size of four will be used. The randomisation is based on sex-specific random list to achieve stratification for gender. The random lists will not be visible to the study personnel involved in recruitment, clinical appointments, sample collection, laboratory analyses and data evaluation.

Study Formula Random Numbers contain 3 digits and are sex-specific:

- Numbers for **girls** start with (uneven hundred number) 101 up to 199 and proceeding with 301
- Numbers for **boys** start with (even hundred number) 201 up to 299 and proceeding with 401

The investigator will receive a list with the ascending Random numbers for boys and girls that shall be followed carefully to assure data meet the assumptions necessary for statistical analysis (Appendix 15.23). If it is decided that the subject will be formula-fed, it will receive the next available study formula random number from the respective sex-specific random list. One by one consecutively Study Formula Random Number has to be given to the subjects. Used Study Formula Random Numbers should be scratched out on the Random number list.

The assignment of the Study Formula Random Number must be documented carefully in the Subject Randomisation List, the Subject Identification List as well as in the individual CRF.

Subjects assigned to the reference breastfeeding group will not receive a Study Formula Random Number; during the course of the study they will only receive a Subject ID Number. Subject ID Number is given to each enrolled subject after informed consent is received.

The Study Formula Random Number will **not** replace the Subject ID Number of the subject. All blood samples and Visit documentation sheets (CRFs) will still be coded by the Subject ID Number primarily. For subjects in one of the formula groups the Study Formula Random

Number will be recorded in addition to the Subject ID Number during all Visits following the randomisation plan ("RANDOM NUMBERB CHART" (Girls/Boys)). At the end of the study the kind of formula given to a subject can be identified with the Study Formula Random Number.

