### **6.1.5 Blinding technique**

All study formula will be blinded by the sponsor according to study design. The products will be packed in identical white boxes and labelled with the same product name. The different standard solution is not written on the package - to achieve an equal dosage table, different spoons will be provided for each subject.

The identity of the specific product will be blind to subjects, support staff and investigators.

Formula boxes and spoon packages are marked with specified Study Formula Random Number (chapter 9.6).

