Subject finally assigned for the formula groups will receive a Formula Random Number as well (chapter 9.6). This number will not replace the Subject ID Number. The Formula Random numbers are 3 digit numbers which will be assigned in ascending order, for girls starting with 101 continuing to 199 and going on with 301. For boys starting with 201 to 299 and proceeding with 401. All subjects finally enrolled (including breastfed infants without Formula Random number) will be documented without contact details in the “Subject Randomisation List”.

Randomisation will be done at best at the Baseline Visit, but can be done until day 14 if parents/caregivers decide -due to any reason not related to this study- to skip breastfeeding during this time. All mothers will be provided with the information that if they against all recommendations decide to stop breastfeeding their infant can be randomised into one of the study formula groups until day 14 of life. Later on they might also be randomised based upon decision of the Principal investigator when the Principal investigator makes sure that mother will be able to fulfil a complete change to study formula not later than day 28.

The Principal Investigator and his study team will do all efforts to enrol a total of 300 subjects within one year – but within 1 ½ year the latest.

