### **8.9 Breaking the code**

The investigator will receive a set of sealed envelopes containing product identification.

The envelopes may be used in circumstances when the investigator identifies an urgent need to break the code. In such cases the rationale must be documented on the corresponding envelope, with immediate notification of the monitor.

The code break will also be reported in the CRF and events leading to the emergency breaking will be recorded in the serious adverse events report form. Code Break must also be documented in the protocol violation form (Appendix 15.22) as this is defined as a protocol violation.

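### Section 9.6 discloses one fixed block length of four to the single recruiting site, so every arm that becomes known gives away some information about its block-mates (minor, cheap to improve)

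*Protocol*

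**What the plan says.** Section 9.6 describes the method: "The study formula randomisation will be a permuted-block design to achieve equal numbers in each group". It gives the length, "A block size of four will be used", and the stratification, "The randomisation is based on sex-specific random list to achieve stratification for gender". Girls' numbers run from 101 to 199 and then from 301. Boys' numbers run from 201 to 299 and then from 401. The investigator holds the ascending list of numbers (not of arms) and strikes off those used: "One by one consecutively Study Formula Random Number has to be given to the subjects". Section 4.1 states that the study is monocentre.

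The same section conceals the arms: "The random lists will not be visible to the study personnel involved in recruitment, clinical appointments, sample collection, laboratory analyses and data evaluation". Section 6.1.5 adds identical white boxes with one product name and says that product identity is blind to subjects, support staff and investigators.

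Three other places bear on whether an arm can become known, or the knowledge used:

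- Section 8.9: "The investigator will receive a set of sealed envelopes containing product identification". They are for urgent need only, and each break is documented and counted as a protocol violation.
- Section 6.1.5: "different spoons will be provided for each subject", so that both products can share one dosage table.
- Section 8.4, on families who decide after day 14: "Later on they might also be randomised based upon decision of the Principal investigator", provided a complete change to study formula is possible by day 28.

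**The concern.** Hiding the arm list protects allocation only while single arms stay unknown. Once an arm is known, the block structure carries information about its neighbours, and the amount depends on how much the site knows of that structure. Here the site is told the exact length and uses the numbers in order. If each list opens a block at its first number, the boundaries are plain: 101–104, 105–108, 201–204 and so on.

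Two things are at stake. First, a predictable next allocation could influence whether or when a late-deciding infant is randomised, since that step rests on the Principal Investigator's decision. Second, a code break partly unmasks up to three block-mates who may still be under follow-up. The site team weighs them for the primary outcome, and under section 10.2.1 the Principal Investigator judges whether their adverse events are related to the formula. Printing the block length does nothing for the site that would offset this.

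**Working it through.** The protocol gives no figure for predictability, so there is none to reproduce.

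**Inputs.** Block length 4, ratio 1:1, sex-specific lists and consecutive use (section 9.6); one site (section 4.1); 200 randomised infants, 100 per formula arm (section 4.2). Assumption: each list starts a block at its first number. The share of arms that becomes known, f, is not in the documents and is varied below.

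**Step 1. What known arms reveal within a block.** There are 6 equally likely sequences of two and two.

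- One arm known: of the other three places, two belong to the opposite arm. Each block-mate is 2/3 = 67% likely to be in the other arm, against 50% before. None is certain.
- Two arms known: they are alike with probability 1/3, and then the other two are fixed. If they differ, the other two are back at 50%.
- Three arms known: the fourth is fixed.

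**Step 2. The ceiling, with every earlier arm known.** The probability that the next allocation is certain is 0, 0, 1/3 and 1 for places 1 to 4.

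- Certain share: (0 + 0 + 1/3 + 1)/4 = 1/3 = 33.3%, or 66.7 of 200.
- Best guess: (1/2 + 2/3 + 2/3 + 1)/4 = 17/24 = 70.8%.

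**Step 3. Only a random fraction f of arms known.**

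- Place 3 is certain if both earlier arms are known and alike: f² × 1/3.
- Place 4 is certain if all three earlier arms are known (f³), or if exactly two are known and alike (3f²(1 − f) × 1/3 = f²(1 − f)). Together this is f².
- Share over the block: (f²/3 + f²)/4 = f²/3.

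| f (assumed) | Next allocations certain | Of 200 |
|---|---|---|
| 0% | 0% | 0 |
| 5% | 0.08% | 0.2 |
| 10% | 0.33% | 0.7 |
| 20% | 1.3% | 2.7 |
| 50% | 8.3% | 16.7 |
| 100% | 33.3% | 66.7 |

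**Step 4. Varied lengths, at the same ceiling.** This was simulated for lists of 100, with every earlier arm known. The observer also knows which lengths are possible, but not their order.

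| Scheme | Certain | Best guess |
|---|---|---|
| Fixed 4 | 33.3% | 70.8% |
| Random 4 or 6 | about 5% | about 69% |
| Random 4, 6 or 8 | about 2% | about 68% |

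Varying the lengths therefore removes most of the certainty and little of the guessing advantage.

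**The case against.** The strongest reply is that the trial is double-blind, so the information needed to exploit the blocks should seldom exist. Boxes are identical, arm lists are hidden from everyone at the site, and each infant has an individual number, so one recognised infant does not decode a shared label. Envelopes are opened only in urgent need and with notice to the monitor, and it would take two or three breaks in the same block to fix an allocation. Late randomisation is tied to feeding feasibility, and the next number must be used. Amendment No. 3 states that clinical personnel had no access to the list of random numbers. A small fixed block also serves the stated aim of equal groups.

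Most of this stands, and it limits the size of the point. It rules out three stronger readings that a reader might infer:

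- *One known arm reveals its block-mates.* It does not. It moves the odds from 1/2 to 2/3 and makes nobody certain.
- *A third of allocations can be deduced.* That holds only if every earlier arm is known, as in an open-label trial.
- *The spoons identify the arm.* Section 6.1.2 describes the study spoons as light blue, without distinguishing the arms, and has them supplied in a closed, numbered envelope. Nothing says that staff can tell which spoon belongs to which formula. Recognition is possible but not shown.

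What the reply does not provide is a reason to print the length. Code breaks are foreseen by the protocol, and each one tells the site more about other infants than it needs to.

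**Conclusion.** The point holds as a minor, avoidable weakness. Nothing in section 9.6 is contradictory or miscalculated. A single disclosed block length, consecutive numbers and one site mean that each unmasked infant shifts the odds for up to three others from 50% to 67%. The chance that a next allocation becomes certain is about 0.1% to 1.3% if 5% to 20% of arms become known, nil if none do, and 33% at the ceiling. These figures assume that each list opens a block at its first number and that arms become known at random across the list. The documents give no rate of unmasking. They offer no evidence that allocation was steered, and none should be inferred.

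**What to change.** Generate each sex-specific list with randomly varied block lengths, for example 4, 6 and 8. Delete the sentence that states the length from section 9.6, and keep the lengths only in the restricted randomisation file held by whoever generates the list. Keep the stratification by sex and the consecutive use of numbers.

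The cost is one parameter when the list is generated and one deleted sentence. The downside is that the largest transient imbalance within a sex list rises from 2 to 4 (half the longest block), which is small against about 100 randomised infants per sex.

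The gain should not be oversold. Even with the possible lengths undisclosed, one known arm would still leave each block-mate more likely than not to be in the other arm: 3/5 in a block of six and 4/7 in a block of eight. The change mainly removes certainty.

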### **9.7 Management of subject withdrawal**

Drop outs will not be replaced as a drop-out rate of 30% is already included in the power calculation. Subjects classified as Drop outs (definition see Chapter 5.5.3) must be documented in the "Withdrawal sheet" at the end of the CRF.

### **9.8 Data management**

All clinical data will be recorded in CRFs to be incorporated later into an electronic database with double data entry. The results of the laboratory analyses will be transcribed from lab print outs by double entry into the same database.

Entered data will be checked on plausibility and internal consistency. For this purpose anthropometric measurements will also be expressed as z-scores relative to the growth standards of the World Health Organization for breastfed children. Z-scores will be calculated using WHO programs (<http://www.who.int/childgrowth/software/en/>). Extreme weight, length and head circumferences as defined by large standard deviation scores will be discarded as implausible:

Weight-for-age z-score (zwei)  $zwei < -6$  or  $zwei > 5$ ,

Length-for-age z-score (zlen)  $zlen < -6$  or  $zlen > 6$ ,

Weight-for-length/height z-score (zwfl)  $zwfl < -5$  or  $zwfl > 5$ ,

BMI-for-age z-score (zbmi)  $zbmi < -5$  or  $zbmi > 5$ ,

Head circumference-for-age z-score (zhc)  $zhc < -5$  or  $zhc > 5$ .

### **9.9 Statistical analysis**

For all quantitative parameters determined a test for normal distribution will be performed according to Kolmogorov-Smirnov. If normal distribution can be assumed, mean and standard deviation will be given for these parameters. For non-normally distributed data median and interquartile range will be provided and data will be transformed appropriately prior to statistical analysis.

For the primary analysis breastfed children will not be included. They serve rather as a reference for the interpretation of the data collected in the formula groups.

The influence of the study group on the primary outcome will be tested using linear regression with baseline values as co-variables. Parameters, which might influence anthropometric development of the infant, e.g. gender, parental smoking and socio-economic status, will be tested for their effect on the outcome variable and, if appropriate, will be included as confounding factors.

Interim analyses are not foreseen as valuable results can not be expected from analysing the data from a limited number of subjects and an association of increased risk of occurrence of adverse events with any of the studied formulas is not conceivable.

Statistical analyses will be performed on the data collected from all infants enrolled into the study and randomised to one of the formulas (intention to treat analysis) and on the data collected from all subjects, who completed the study according to the protocol (per-protocol analysis). The per-protocol analysis is considered the primary analysis; the intention-to-treat analysis has confirmative character.

Full analysis (Intention-to-Treat = ITT Principal) comprises all subjects who were enrolled including those with minor and severe non-compliance to protocol, subjects with missing values (but who participated at least in Visit 1) and protocol violations. Solely subjects turned out to be a "screening failure" (does not fit to an important inclusion or exclusion criteria) will not be considered for full analysis.

The Per-Protocol Population (PPP) is defined as the set of subjects without severe non-compliance to the protocol. Minor non-compliance e.g. visit outside the given window, or missing values of marginal importance (stool colour not reported once) are acceptable and do not lead to exclusion from the PPP analysis.

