### 9.2 Hypothesis to be tested

$H_0$  (to be rejected): The mean daily weight gain in the intervention group (formula with reduced protein content) is more than 3 grams per day lower than in the control group (standard formula).

$H_{\text{alternative}}$ : The mean daily weight gain in the intervention group (formula with reduced protein content) is not more than 3 grams per day lower than in the control group (standard formula).

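### The per-protocol analysis is primary and the intention-to-treat analysis has no stated decision role, although about 15% of infants are expected to switch formula and leave the per-protocol set

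*Protocol*

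**What the plan says.** Section 9.2 sets the only success criterion. The null hypothesis is that mean daily weight gain in the intervention group "is more than 3 grams per day lower than in the control group". It names no analysis set.

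Section 9.9 plans two analyses. One is intention to treat: "Statistical analyses will be performed on the data collected from all infants enrolled into the study and randomised to one of the formulas". The other is per protocol. Their ranking is: "The per-protocol analysis is considered the primary analysis; the intention-to-treat analysis has confirmative character". Nothing further is said about how the second result bears on the conclusion.

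Section 9.5 expects 10-15% true loss to follow-up and that "another 15% will switch formula due to preference changes which usually take place in the first months of life". It adds: "These children will be only available for an intention-to-treat analysis". The definitions agree with this. Section 5.4.1 rules out any other formula, section 5.5.1 classes feeding outside the definition of full feeding as severe non-compliance, and sections 5.5.2 and 9.9 keep severe non-compliance out of the per-protocol set.

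**The concern.** The primary set is formed after randomisation, and the plan itself expects it to lose a sizeable group. If the reason for switching is unrelated to growth, nothing is lost but precision. If slow growth or poor acceptance leads to a switch, and does so more in one arm, the per-protocol difference is biased. Should it happen mainly in the low-protein arm, the bias favours non-inferiority.

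The intention-to-treat analysis would expose this, but calling it confirmative is not a decision rule. If the per-protocol limit clears -3 g/d and the intention-to-treat limit does not, nothing in the protocol prevents a claim of non-inferiority. That claim supports the suitability of a formula below 2 g protein/100 kcal (section 3), so the rule that decides it matters.

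**Working it through.** **Inputs from the protocol.** Margin 3 g/d (9.2). Mean and SD of weight gain: "30 grams per day with a standard deviation of 6 grams between birth and 4 months of life" (9.5). One-sided 2.5%, power 85%, about 70 evaluable and 100 enrolled per arm, loss 10-15%, switching 15% (9.5).

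**Assumptions, not in the protocol.** The correlation ρ between slow growth and switching, how switching is spread over the arms, and growth after a switch.

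**Step 1: the plan's own figure.** n = 2 × [6 × (1.960 + 1.036) / 3]² = 71.8, so 72 per arm against the stated figure of about 70. Power with 70 is 84.1%, and 70 / 0.70 = 100. The sample size reproduces.

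**Step 2: the sets.** 100 - 15 lost = 85 followed per arm, and 85 - 15 switched = 70 per protocol. Switchers are 15/85 = 17.6% of those followed.

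**Step 3: bias if selection acts in the study arm only.** Let the 17.6% lowest on a latent score with correlation ρ to growth switch. The normal cut-off is -0.929 with density 0.259, so the mean of those who stay rises by 6 × ρ × 0.259 / 0.824 = 1.89ρ g/d. The standard error with 70 per arm is 6 × √(2/70) = 1.014. At a true difference of -3, false success is Φ(1.89ρ / 1.014 - 1.96):

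- ρ = 0: 2.5%
- ρ = 0.3: shift 0.57, 8.1%
- ρ = 0.5: shift 0.94, 15.2%
- ρ = 0.65: shift 1.23, 22.7%

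Simulation (20,000 trials per scenario), which also picks up the smaller spread among those who stay, gives about 8%, 16% and 24%.

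**Step 4: other patterns of switching.** Per-protocol false success, true difference -3 g/d, SD 6:

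| Assumed pattern | ρ = 0.3 | ρ = 0.5 | ρ = 0.65 |
|---|---|---|---|
| Equal numbers, equal selection in both arms | about 2-3% | about 2-3% | about 2-3% |
| One common growth-related rule in both arms | 3.0% | 4.7% | 7.7% |
| Selection in the study arm only | about 8% | about 16% | about 24% |

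Under the common rule the slower arm loses more infants (about 20-22% against 14-16%). A further run put the upper end of that row near 9%. With 20% against 10% switching and ρ = 0.5 in both arms, the rate is 6.7%.

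**Step 5: requiring both analyses.** If switching does not itself change growth, the combined rule gives at most about 2.7% in every scenario run. If switched study-arm infants recover the whole 3 g/d (an upper bound), the intention-to-treat difference moves by 3 × 15/85 = 0.53 g/d. With standard error 6 × √(2/85) = 0.920, its own error is Φ(0.53 / 0.920 - 1.96) = 8.3% (7.7-9.1% simulated). Under study-arm selection the combined rule then gives 5.9%, 8.1% and 8.7% at ρ = 0.3, 0.5 and 0.65. With half the deficit recovered it gives 4.2-5.0%.

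**Step 6: price.** With equal formulas and switching unrelated to growth, power is 84.0% per protocol, 90.0% by intention to treat and 82.6% for both: 84.0 - 82.6 = 1.4 points.

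**The case against.** The strongest defence is that a per-protocol primary analysis is an accepted choice for non-inferiority, because intention to treat can dilute a real difference when infants change formula. That stands: the choice itself is not an error. It also argues for using both sets, since each guards against the other's bias.

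A reader might infer that the plan lets the per-protocol result override a contrary intention-to-treat result. The text does not say so. Both analyses are planned and a split result is simply not addressed. A rule for disagreement could sit in an analysis plan that is not at hand. But the protocol does fix the ranking of the two sets, and that ranking leaves the second without a decision role.

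A reader might also infer that slow growers are the ones who switch. Section 9.5 names only preference as the reason, section 6.1.5 blinds families and staff, and some switching will fall in the run-in, where section 6.3.1 accepts another formula until Day 27, before the outcome window opens at Visit 1. Blinding makes a growth-driven rule likely to act alike in both arms, which points to the middle row of the table rather than the last. It does not exclude a difference: the formulas differ in protein, fat blend and added oils (6.1.1), so acceptance, which section 7.3.6 records, could differ by arm.

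**Conclusion.** The concern holds in a limited form. The protocol ranks the per-protocol analysis first, expects about 15% of infants to leave it by switching, and states no consequence if the intention-to-treat analysis fails the margin. The false non-inferiority rate stays near 2.5% when switching is unrelated to growth or selects equally in both arms. It is about 3-9% under a common growth-related rule and about 8-24% only if selection is confined to the study arm.

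These figures rest on assumed correlations of 0.3 to 0.65, 85 followed and about 15 switching per arm. A reader might take 24% as the trial's error rate. The documents do not support that, because they give no correlation and no difference between arms. Nor would it be right to say that requiring both analyses restores 2.5%: that needs switching to leave growth unchanged. The rule is a cheap improvement, not the repair of a fatal fault.

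**What to change.** In section 9.9, state that non-inferiority is concluded only if the lower limit of the two-sided 95% confidence interval for study minus control lies above -3 g/d in both the per-protocol and the intention-to-treat analysis. State that infants who switch formula are still weighed at Visit 4 and analysed in the arm to which they were randomised, and that a split result is reported as non-inferiority not shown.

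Both analyses are already planned, and switching is not among the drop-out reasons in section 5.5.3, so follow-up of these infants fits the existing design. The cost is a short addition to the text and about 1.4 points of power if the formulas are equal (84.0% to 82.6%). The remaining weakness is dilution: if switched study-arm infants recover growth, the error of the combined rule can still be about 4-9%. Reporting the number, timing and reasons of switches by arm would let readers judge that.
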